### Sample size

It is estimated that between 240 to 384 patients with gastroschisis will present to the seven study centres during the 2-year data collection period (
Table 4). An estimated 75% of the neonates with gastroschisis should fulfil the inclusion criteria within the context of the study sites, equating to between 180 and 288 patients in the study in total (67–109 pre-intervention and 113–179 post-intervention). A successful pre-hospital component of the study may result in more patients presenting with simple gastroschisis and hence more being eligible for study inclusion.

**Table 4. T4:** The estimated number of gastroschisis cases per month at each of the study centres.

Site	Estimated no. cases/month	Dates for pre- intervention data collection at each site (total no. months)	Minimum no. pre-intervention cases,	Maximum no. pre- intervention cases	Timeframe for intervention implementation at each site in 2019	Dates for post- intervention data collection at each site (total no. months) *	Minimum no. of post- intervention cases	Maximum no. of post- intervention cases
**Korle-Bu TH,** **Ghana**	1	Oct 2018–May 2019 (7 months)	7	7	May 13 ^th^ – June 7th	May 2019 – Oct 2020 (17 months)	17	17
**Tamale TH, Ghana**	1–2	Oct 2018–June 2019 (8 months)	8	16	June 10 ^th^ – July 5th	June 2019 – Oct 2020 (16 months)	16	32
**Komfo Anokye TH,** **Ghana**	1	Nov 2018–July 2019 (8 months)	8	8	July 8 ^th^ – Aug 2nd	July 2019 – Nov 2020 (16 months)	16	16
**University TH** **Lusaka Zambia**	2–4	Nov 2018–August 2019 (9 months)	18	36	August 12 ^th^ – Sept 6th	Aug 2019 – Nov 2020 (15 months)	30	60
**ADCH, Zambia**	1	Jan 2019–Sept 2019 (8 months)	8	8	September 16 ^th^ – Oct 11th	Sept 2019 – Jan 2021 (16 months)	16	16
**KCH, Malawi**	2–4	Dec 2018–Oct 2019 (10 months)	20	40	October 21 ^th^ – Nov 15th	Oct 2019 – Dec 2020 (14 months)	28	56
**MNH, Tanzania**	2–3	Jan 2019–Nov 2019 (10 months)	20	30	Nov 25 ^th^ – Dec 20 ^th^	Nov 2019 – Jan 2021 (14 months)	28	42
**TOTAL**	**10 – 16**	**60 months**	**89**	**145**	**8 months**	**108 months**	**151**	**239**
**No. of patients** **with simple** **gastroschisis**	**8–12**		**67**	**109**			**113**	**179**

*Each site will collect 24 months of data in total

In this study a convenience sample has been used and hence a post-hoc power calculation has been undertaken. Utilising a two-sided Z-test it has been calculated that at 90% power and p=0.05, the study could detect a difference in mortality of 16% (95% mortality down to 79%) if the minimum number of patients were included and a difference of 12% (95% mortality down to 83%) with the maximum estimated number.

This indicates that the study is appropriately powered. Some centres within sub-Saharan Africa have achieved a mortality rate of 80% or less, suggesting it is an achievable target.

## Stages of implementation

This will involve four key stages: 1) exploration, 2) preparation, 3) implementation, 4) sustainment
^126^.

### 1) Exploration stage

***Context.*** A good understanding and consideration of the local context is vital for the success of the project
^127^. Preliminary data has been collected from study team members through online written correspondence, video meetings and a literature review, as summarised in the Introduction above
^79–
105^. Identified key facilitators and barriers for study success are summarised below and will be further investigated through the systematic review, qualitative study, Delphi process and local in-person co-development meetings. In addition, an institutional capacity assessment will be undertaken at each study site to determine the resources currently available for gastroschisis management (
Supplementary File 3)
^110^. The interventional bundle and implementation strategy will be adapted to overcome such barriers and optimise facilitators.

Summary of key facilitators:

Local champions with a strong desire to improve outcomes.Self-selected teams who have requested to participate in the study.The availability of a low-technology, cost-effective interventional bundle with proven effectiveness.One to four cases per month at the study sites with a current mortality of over 90–95% and hence the potential to significantly improve outcomes.

Summary of key barriers:

Staff shortages, particularly nursing staff.Staff culture and current beliefs regarding the futility of neonates with gastroschisis
^2,
6^.Lack of infrastructure for the provision of neonatal PN and resources for central IV access.Problems with infection control and sepsis.

Key strategies to overcome barriers:

Involvement of all key members of the MDT in the development of the interventional bundle to ensure it is acceptable and feasible within the local contexts.Utilisation of maternal input for monitoring, basic care and identification of red flags to help overcome nursing shortages, in centres where it is deemed appropriate.Empowerment of nurses through training, resource provision and inclusion in all aspects of the study development, implementation and follow-up. This will include group and one-on-one training and in-practice support from a surgical nurse specialist with experience managing neonates with gastroschisis.MDT simulation training to optimise teamwork, networks and solidarity around a shared goal to improve survival in neonates with gastroschisis.Input from a paediatric gastroenterologist specialised in PN to identify and trial potential solutions to sourcing and administration of PN for neonates at the study sites. Lessons will be learned from experts managing to administer PN successfully in low-resource environments from the qualitative study analysis.Implementation of a standardised protocol of care with proven infection control measures that have been successful in LMIC QI projects.

***Pre-intervention data collection.*** This will determine the current management strategies and the pre-intervention outcomes, both of which are vital to measure and evaluate change. Ineffective or potentially harmful strategies identified through evaluation of the pre-intervention data can be discussed amongst the MDT team and targeted for improvements during the intervention phase.

### 2) Preparation stage

***In-country co-development meeting.*** The preparation and implementation stages are outlined in
Figure 1. Upon arrival at each study site, the PI will meet with the study lead and key stakeholders. A co-development meeting will be held within the first week with all members of the MDT caring for neonates with gastroschisis and other key stakeholders such as hospital management. The study details will be presented, discussed and debated. Adaptations will be made according to the local context as advised by the team. Required resources will be sourced and purchased (
Supplementary File 4)
^110^. A plan will be made with the local team regarding equipment storage for safe keeping and easy access.

**Figure 1. f1:**
[figure not shown]
In-country implementation timeline (4-week period).

***Training***. A training timetable will be devised. Initially, there will be a training day for all MDT members which will include:
1) Initial resuscitation, silo application, reduction and closure using a gastroschisis simulation model.2) MDT simulation training where all team members practice managing a neonate with gastroschisis in real time from the point of arrival at hospital to silo application and stabilisation.3) Daily ward management and care (with a nurse training session led by a surgical neonatal nurse specialist with experience managing neonates with gastroschisis).4) Early breastfeeding and enhanced enteral feeding programme.5) Infection control and central line management.6) Parenteral nutrition prescribing, preparation, safe administration and storage (if it is going to be included in the interventional bundle at that site).7) Parental involvement in neonatal monitoring and care.8) Patient consent.

The trainers will include the principal investigator (paediatric surgery registrar with experience managing neonates with gastroschisis and use of a preformed silo for reduction and sutureless closure), a neonatal nurse specialist (with experience managing neonates with gastroschisis and infection control), and a paediatric gastroenterologist (specialised in enhanced enteral feeding programmes and parenteral nutrition). The course will be designed by these three healthcare professionals with input from the study leads and lead investigators. Teaching methods will include a combination of didactic and interactive presentations and group simulation training. The latter will utilise a gastroschisis simulation model along with the basic equipment required to resuscitate a neonate with gastroschisis to replicate the real-life situation as much as possible. There will be a pre- and post-training evaluation to identify further training needs that can be undertaken during the 4-week implementation phase (this will not be an assessment, rather a strategy to optimise protocol uptake and fidelity).

***Pre-hospital component.*** A further meeting with the study lead and appropriate stakeholders will be undertaken to confirm details of the pre-hospital component. Key stakeholders from the gastroschisis referral centres surrounding the study centre will be identified and a context-specific implementation strategy developed to implement the pre-hospital management protocol.

### 3) Implementation stage

***Further training and support.*** The PI will spend a total of 4 weeks at each site. During this time the PI will attend every admission and in-hospital delivery of a neonate with gastroschisis to assist the local team with implementation and use of the study protocol. This will include an estimated one to four neonates at each site according to current presentation rates. The PI will attend daily neonatal ward rounds, provide input on patients with gastroschisis on the ward on a daily basis, attend twice-daily silo reductions and be present during ward closures.

A surgical nurse specialist will spend two weeks at each study site, initially to help with the MDT training day and then to spend time on the wards with the nurses in order to assist with in-practice, real time training. Additional training sessions can be planned during this time as required. The aim will be to empower the nurses through resource allocation, training and encouragement from a nurse who regularly successfully manages neonates with gastroschisis.

A paediatric gastroenterologist will spend two weeks at each site to assist with the MDT training day, work with the local team to develop the infrastructure and skills required to provide PN (if included in the protocol at that site) and to provide training on an enhanced enteral feeding programme.

***Pre-hospital component.*** This will be undertaken by the PI and key stakeholders during the 4 week in-country period.

### 4) Sustainment stage

***Monthly MDT feedback and troubleshooting meetings.*** The initial meeting will happen within two weeks of managing the first neonate with gastroschisis following implementation of the protocol and then at monthly intervals thereafter for the duration of the study. When in-country the PI will attend the meeting personally; following that the PI will attend remotely via teleconference. At the meeting a real time update on outcomes will be fed back to the MDT, both the patient outcomes and compliance with the protocol (fidelity). There will be the opportunity to trouble-shoot and decide upon potential solutions to problems encountered. Meetings will be postponed to the following month if no neonates with gastroschisis were managed at the study centre during the preceding month.

## Data collection

### Clinical outcomes

***Primary outcome.***

1) All-cause, in-hospital mortality.

***Secondary outcomes.***

1)   Major complication within 30-days of primary intervention
^1^: secondary bowel ischaemia, necrosis or perforation requiring resection
^2^, abdominal compartment syndrome
^3^ or need for further unplanned surgical intervention.

2)   Length of hospital stay amongst survivors (days).

3)   Time to full enteral feeds (days).

4)   Need for ventilation (yes/ no).

5)   Duration of ventilation (within 30 days of primary intervention in days).

Patient data will be collected on patient demographics, antenatal care, pre-hospital care, clinical condition on arrival, resuscitation, intervention (for bowel reduction and closure), ward care and outcomes (
Supplementary File 5)
^110^.

***Study impact on neonates with other congenital anomalies.*** The all-cause in-hospital mortality pre- and post- intervention will be determined for neonates presenting for the first time with anorectal malformation and intestinal atresia to see if there are indirect benefits for other patients requiring a similar package of neonatal surgical care.

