## Data analysis

### Clinical outcomes

***Pre-post study analysis.*** Primary and secondary clinical outcomes will be compared pre- and post-intervention using chi-squared analysis for categorical variables or Fisher’s exact test if either of the groups contains less than 10 patients. For normally distributed continuous variables an unpaired t-test will be used and for non-normally distributed continuous variables a Mann-Whitney
*U* test will be used. P<0.05 will be deemed significant. Cases presenting during the 1-month implementation phase will be deemed post-intervention since the PI will be in attendance at all cases alongside the local team to assist with implementation of the protocol and training will have commenced.

***Time series analysis.*** Time series analysis will be undertaken using Statistical Process Control to distinguish significant trends and shifts in mortality from background variation during the study period
^134^.

***Multivariate analysis.*** Multivariate logistic regression analysis will be used to identify factors affecting all-cause in-hospital mortality with adjustment for confounding factors. Potential confounders include gestational age, weight, presence of co-morbidities, and ASA score at the time of primary intervention.

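### Four secondary outcomes are tested between periods with no handling of death beyond restricting length of stay to survivors, so improved survival by itself can shift them

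*Protocol article*

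**What the plan says.** Under Secondary outcomes, the protocol article lists "Major complication within 30-days of primary intervention" (bowel loss needing resection, abdominal compartment syndrome or unplanned surgery; death is not a component), "Length of hospital stay amongst survivors (days)", "Time to full enteral feeds (days)", need for ventilation, and "Duration of ventilation (within 30 days of primary intervention in days)".

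Under Data analysis, Clinical outcomes, the comparison is fixed: "Primary and secondary clinical outcomes will be compared pre- and post-intervention using chi-squared analysis for categorical variables", with Fisher's exact test when a group has fewer than 10 patients. For the rest, "For normally distributed continuous variables an unpaired t-test will be used and for non-normally distributed continuous variables a Mann-Whitney" U test applies, and "P<0.05 will be deemed significant".

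The survivor restriction on length of stay is the only reference to death in these definitions. The logistic regression and time-series analyses that follow concern mortality, and fidelity in the sustainability analysis, so they do not deal with death in the secondary outcomes.

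**The concern.** The article plans for 95% mortality before the bundle. In the literature that its Introduction cites for low- and middle-income settings, most deaths come early, at a median of 4 days. Median length of stay for simple gastroschisis in high-income countries is given as 36 days. Most pre-period neonates would therefore be dead before discharge or full feeds could happen.

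Two mechanisms follow:

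- **Selection.** Length of stay, and in practice time to full feeds, is observed only in survivors. The bundle is meant to enlarge that group, so the two sets of survivors need not be alike.
- **Truncation.** A neonate who dies on day 4 contributes four days in which a complication or a ventilated day can be recorded. One who lives contributes up to thirty. Better survival lengthens exposure even when the daily risk is unchanged.

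The article's section on unintended consequences names more complications and longer stays as possible harms of the bundle. The planned tests cannot separate those harms from the effect of neonates living longer, and the results are meant to inform scale-up.

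**Working it through.** **Inputs from the article.** Group sizes are 67 and 113 (minimum) or 109 and 179 (maximum), from Sample size. Mortality is 95% before, and 79% (minimum) or 83% (maximum) after, from the power statement. Median time to death is 4 days, from the Introduction; that figure covers simple and complex cases together and is counted at a healthcare facility.

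**The plan's own figure.** An arcsine two-sided z-test at 0.05 reproduces the stated detectable differences: power is 90.1% for 95% against 79% (67 and 113), and 90.7% for 95% against 83% (109 and 179). The planning values are used below as they stand.

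**Step 1: survivors available.** Expected survivors = n × (1 − mortality).

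| Scenario | Pre | Post |
|---|---|---|
| Minimum | 67 × 0.05 = 3.4 | 113 × 0.21 = 23.7 |
| Maximum | 109 × 0.05 = 5.5 | 179 × 0.17 = 30.4 |

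The binomial chance of fewer than 3 pre-period survivors is 34% (n = 67) or 9% (n = 109). At 90% baseline mortality, the lower end of the site criterion, the expected pre-period numbers are 6.7 and 10.9.

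**Step 2: what a survivor-only test can detect.** The normal approximation, (1.960 + 0.842) × √(1/n₁ + 1/n₂), gives 2.802 × √(1/3 + 1/24) = 1.72 SD and 2.802 × √(1/5 + 1/30) = 1.35 SD. The t-distribution calculation gives 1.79 and 1.39 SD at 80% power. Power for a 0.5 SD difference is 12% and 17%.

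**Step 3: complications with an unchanged hazard.** Assumptions: constant complication hazard h, equal in both periods; 30-day risk r if alive throughout, so h = −ln(1 − r)/30; deaths exponential with rate λ = ln 2/4 = 0.1733 per day. A neonate who dies has a recorded complication with probability q = h/(h + λ) × [1 − exp(−30(h + λ))]. With mortality m, the observed proportion is m·q + (1 − m)·r.

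| Assumed r | h per day | q | Pre, m = 0.95 | Post, m = 0.79 |
|---|---|---|---|---|
| 5% | 0.00171 | 0.97% | 1.2% | 1.8% |
| 10% | 0.00351 | 1.98% | 2.4% | 3.7% |
| 30% | 0.01189 | 6.40% | 7.6% | 11.4% |

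For r = 30%: pre is 0.95 × 0.0640 + 0.05 × 0.30 = 0.076; post is 0.79 × 0.0640 + 0.21 × 0.30 = 0.114.

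**Step 4: ventilation days.** Assume that a ventilated neonate's need would last an exponential time with a median of 10 days, cut off by death or day 30. With v = ln 2/10 = 0.0693, mean recorded days are [1 − exp(−30(v + λ))]/(v + λ) = 4.1 in those who die and [1 − exp(−30v)]/v = 12.6 in those who live. The overall mean is 0.95 × 4.1 + 0.05 × 12.6 = 4.5 pre and 0.79 × 4.1 + 0.21 × 12.6 = 5.9 post. With an assumed median of 5 or 20 days, the same formulas give 3.4 to 4.0 and 5.5 to 7.7.

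**Step 5: chance of a misleading test.** In simulations on the Step 3 and 4 assumptions (10-day median, half of neonates ventilated), a significant result against the bundle appeared in about 9% to 12% of trials at the protocol's target effects. For complications at r = 10% it was 3% to 5%.

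**The case against.** The strongest reply is that these are secondary outcomes, the mortality comparison is untouched, and mortality will be there to qualify them. That stands, and it limits the seriousness of the point.

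Several narrower objections also stand:

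- A reader might infer that about 95% of pre-period neonates die before any of these outcomes can be seen. That is strict only for discharge and full feeds. A complication or a period of ventilation can precede death.
- A reader might infer that survivor length of stay is bound to look worse after the bundle. Restricting to survivors means early deaths do not shorten pre-period stay. A bias also needs the added survivors to be sicker and to stay longer, which is plausible but not stated in the article.
- Few survivors means imprecision, not bias, and no choice of test changes it. It argues for description rather than testing.
- The 4-day median comes from simple and complex cases together, whereas the trial includes simple cases only and starts its complication window at the primary intervention.
- A condensed article may leave rules for death in the feeding and ventilation outcomes to an analysis plan.

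The last objection does not dispose of the point. The survivor restriction, the complication window without death as a component, and the named tests for all secondary clinical outcomes are written into the article.

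**Conclusion.** The point holds as a should-fix matter. As written, the comparisons condition on survival (length of stay) or are precluded or cut short by death (feeds, complications, ventilation), and survival is what the bundle aims to change.

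The survivor counts and the 1.8 or 1.4 SD detectable differences follow from the plan's own figures. The direction of the shift in complications and ventilation days needs only early deaths and lower post-period mortality, with the underlying risks unchanged. Its size rests on assumed complication risks, ventilation times and timing of death: at 79% mortality the complication shift ranges from 0.6 to 3.8 percentage points over the risks tried.

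The stronger conclusion that the secondary results would be wrong, or that an effective bundle would generally appear harmful, is not supported. At the target effects most simulated trials show no significant result against the bundle.

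**What to change.** In all included neonates:

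1. Analyse discharge alive and full enteral feeds as cumulative incidence from arrival, with death as a competing event.
2. Report major complications as cumulative incidence with death competing, shown beside death, and interpret any rise jointly with mortality. State how neonates who die before any primary intervention are counted.
3. Report survivor-only length of stay and ventilation days descriptively, without a test. Days alive and ventilator-free to day 30 may be added as a supplement.

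The cost is a change of analysis wording plus a recorded date of death. The outcomes as listed do not strictly require that date, and the data collection form is a supplementary file not shown here, so this should be checked. The downside is that discharge-alive and full-feeds results will largely track mortality. If every survivor reached full feeds, the contrast would be 5% against 21% or 17%, which is the primary comparison again. Ventilator-free days would also be dominated by death. These results should be presented as such, not as independent evidence of benefit.

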### Implementation of the interventional bundle

***Study design.*** A hybrid type 2 effectiveness-implementation pre-post study design will be utilised, which focusses equally on the effectiveness of the intervention through analysing clinical outcomes and effectiveness of the implementation through analysis of the service delivery and implementation outcomes
^111^.

The theoretical underpinning of the intervention and implementation strategy is based on the normalisation process theory (NPT)
^112^. This is a theory developed by implementation researchers in order to provide explanation and understanding of how a novel intervention becomes standard practice within a healthcare setting
^113–
115^.
Table 2 highlights the four constructs of the NPT and how they are addressed in the study design. The associated validated survey, NoMAD, will be utilised to evaluate MDT members opinions on each of these four areas at the end of the MDT training day (detailed below) and deficient areas will be actively targeted for improvement during the 4-week in-country implementation phase (
Supplementary File 2)
^110,
116^. The survey will be repeated at the end of the study to assess if and how perceptions have changed between implementation and study completion.

**Table 2. T2:** Normalisation process theory constructs used in the study design.

Normalisation Process Theory Constructs	How these will be addressed in the study
**Coherence:** • Participants distinguish the intervention from current ways of working • Participants collectively agree about the purpose of the intervention • Participants individually understand what the intervention requires of them • Participants construct potential value of the intervention for their work	• Involvement of all key MDT members in the development of the study and interventional bundle to be implemented • MDT simulation training (detailed below) • Through raising awareness about the possibility of improved outcomes using examples from other LMIC settings (through sharing the results of the systematic review and qualitative study with MDT members and discussion during the Delphi process consensus meeting, in-country co-development meeting and MDT training day). A leaflet will be developed and distributed amongst MDT members detailing successful gastroschisis management initiatives in other LMIC settings.

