^132^.

***Coverage.*** The proportion of eligible patients who actually receive the intervention will be determined through the data entered into REDCap on all patients presenting with gastroschisis. Neonates with simple gastroschisis included within the study will have all data points completed. Neonates with complex gastroschisis excluded from the study intervention will have baseline data collected on the following: patient demographics, pre-hospital care and outcomes.

***Cost.*** The average cost per patient with gastroschisis will be estimated at the study centres, pre- and post-intervention. The implementation costs will also be calculated. The number of disability-adjusted life years (DALYs) averted through implementation of the interventional bundle will be calculated. The previously utilised disability-weight of 0.2 will be used for surviving neonates with gastroschisis where 0 is no disability and 1 is death
^2^. The cost in US$ per DALY averted will be calculated.

***Sustainability.*** The current intervention and implementation strategy have been evaluated for potential sustainability using the NHS Quality Improvement Sustainability Model
^133^. It scored 69.5/100 (19.8/31.3 for process, 43.1/52.4 for staff and 6.6/16.5 for organisation). A score above 55 is deemed ‘reason for optimism’. This evaluation has highlighted the need to set up a monitoring process beyond the life of the study, involve organisation leaders throughout the study process, to align the project with the team and organisation’s other strategy aims for improvement and to ensure facilities and equipment utilised are sustainable long-term. A re-evaluation will be undertaken just prior to interventional implementation and again following completion of the study.

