### Unintended consequences

Potential unintended or indirect consequences of the study, both positive and negative, must be considered.

Positive consequences may include:

•   Improved team building/ interaction/ communication with benefits for a wider range of patients.

•   Improved generic neonatal care and resuscitation skills and infection control awareness with potential benefits for a wider range of patients.

•   Development of infrastructure and supply routes required to enable delivery of neonatal PN with benefits to a wider range of patients.

•   Enhanced research capacity.

•   Enhanced CV’s and career progression amongst those involved.

•   Greater staff job satisfaction with the potential for improved retention rates.

•   Development of networks with international partners with the potential for future collaborative projects.

Negative consequences may include:

•   Potentially less time with other patients.

•   Disruption of study team members work/life balance.

•   Risk of reduced survival/increased complications in those few (5-10%) with simple gastroschisis who may have survived with primary closure in theatre if available.

•   Risk of prolonged hospital stays and resource utilisation without improved survival.

The above possible negative consequences will be discussed with study team members and a plan instigated to minimise risk. Parents will be informed both in writing and verbally of both the potential benefits and risks associated with participation in the study at the time of consent.

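### Anorectal malformation and atresia mortality is given one reading, indirect benefit, although an uncontrolled pre-post fall cannot be told apart from a general improvement in care over time

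*Protocol article*

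**What the plan says.** Under Data collection, Clinical outcomes (Study impact on neonates with other congenital anomalies), the protocol article states: "The all-cause in-hospital mortality pre- and post- intervention will be determined for neonates presenting for the first time with anorectal malformation and intestinal atresia". The only purpose given is "to see if there are indirect benefits for other patients requiring a similar package of neonatal surgical care". Unintended consequences and Study impact repeat the spill-over idea; the former lists "Improved generic neonatal care and resuscitation skills and infection control awareness with potential benefits for a wider range of patients".

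The design has no control sites: "A hybrid type 2 effectiveness-implementation pre-post study design will be utilised". Under Data analysis, "Primary and secondary clinical outcomes will be compared pre- and post-intervention using chi-squared analysis for categorical variables". The same section plans Statistical Process Control "to distinguish significant trends and shifts in mortality from background variation during the study period" and a multivariable logistic regression, for which "Potential confounders include gestational age, weight, presence of co-morbidities, and ASA score at the time of primary intervention". Calendar time is not among the confounders named.

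Study limitations does not mention secular trend or the lack of a concurrent control. It does say that involving site teams in developing the bundle may change practice before implementation.

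**The concern.** A lower post-intervention mortality in these other neonates has at least two explanations. The bundle may have reached them through better generic care, or neonatal surgical care at the sites may have been improving regardless. The first adds to the case for the bundle. The second weakens it, because the same improvement would lower gastroschisis mortality and appear as a bundle effect in the primary test. The protocol asks only about the first, so evidence of a background trend could be reported as a further benefit.

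The opposite result also has a use that the protocol does not mention. If mortality in these neonates stayed flat while gastroschisis mortality fell, that would argue against a general improvement in care and strengthen the primary finding.

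**Working it through.** **1. The plan's own figure.** Sample size states 90% power, two-sided p=0.05, for 95% to 79% at the minimum and 95% to 83% at the maximum number of patients. Group sizes are 67 pre and 113 post (minimum), 109 and 179 (maximum). With power = Φ((d − 1.96·SE0)/SE1), where SE0 uses the pooled and SE1 the separate variances:
- 67/113: d = 0.16, SE0 = 0.0551, SE1 = 0.0467, power 86.7%.
- 109/179: d = 0.12, SE0 = 0.0401, SE1 = 0.0350, power 88.1%.
- Equal split of the same totals (90/90 and 144/144): 89.8% and 90.6%.

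The stated 90% reproduces with an equal split. Nothing below depends on the small difference.

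**2. Exposure of the primary test to drift.** Assume no bundle effect and survival drifting from 5% to 10% or 13%. The table gives the exact binomial probability that the pooled Z exceeds 1.96 in favour of the post period.

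| Mortality pre → post | 67/113 | 109/179 |
|---|---|---|
| 95% → 95% | 0.018 | 0.021 |
| 95% → 90% | 0.206 | 0.319 |
| 95% → 87% | 0.418 | 0.624 |

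The normal approximation of step 1 gives 0.20 and 0.31 for the 5-point drift. The documents give no drift size, and a 5-point drift already means survival doubling.

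**3. What could separate the two readings.** Table 4 staggers the starts: 13 May, 10 June, 8 July, 12 August, 16 September, 21 October and 25 November 2019. After the first site switches, the other six contribute about 0.9 + 1.8 + 3.0 + 4.1 + 5.3 + 6.4 ≈ 21 further pre-intervention site-months. Multiplying each term by that site's monthly rate gives roughly 36 to 60 gastroschisis cases of all types. From late November 2019 no site is pre-intervention, so this contrast is limited to about six months.

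Complex gastroschisis is a second same-site series with outcomes: "Neonates with complex gastroschisis excluded from the study intervention will have baseline data collected on the following: patient demographics, pre-hospital care and outcomes". By subtraction in Table 4 there are 89 − 67 = 22 to 145 − 109 = 36 pre and 151 − 113 = 38 to 239 − 179 = 60 post. It is no clean control, since these neonates share the pre-hospital component and Sample size allows that a successful pre-hospital component may shift case mix towards simple cases.

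**4. Why a single net difference is not safe.** The documents give no baseline mortality for the other conditions. Assume 30%, and a common background drift that takes gastroschisis from 95% to 90% with no bundle effect.
- Common odds ratio: (0.90/0.10)/(0.95/0.05) = 0.474. Comparator odds are 0.429 × 0.474 = 0.203, so mortality is 16.9%. The comparator falls 13.1 points and gastroschisis 5, and the bundle looks about 8 points harmful.
- Common risk ratio: 0.30 × 0.90/0.95 = 28.4%. The comparator falls 1.6 points, and the bundle looks 3.4 points beneficial.

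The same drift gives opposite signs depending on the scale.

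**5. Precision of a period-by-condition contrast.** Assume comparator mortality of 20% to 50% and a series one to two times the gastroschisis groups; the documents give neither. Power = Φ(d/√(V1 + V2) − 1.96).
- Lowest: 109/179, 50%, equal size. V1 = 0.00122, V2 = 0.00369, d = 0.12, power 0.40.
- Highest: 67/113, 20%, double size. V1 = 0.00218, V2 = 0.00190, d = 0.16, power 0.71.

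**The case against.** The strongest reply has five parts.

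- **Ancillary purpose.** The protocol asks whether there are indirect benefits; it does not undertake to credit every fall to the bundle. A reader might infer such a commitment, but the text does not contain one. What stands against the plan is that only one reading is named.
- **Trend handling is planned.** Statistical Process Control can show whether gastroschisis mortality was already drifting or shifted at a particular time. It cannot say whether a shift came from the bundle or from another change in care at that time, and Table 4 expects only 1 to 4 cases per site per month. The reply stands in part.
- **Contaminated comparator.** The protocol expects the bundle to help these neonates, so subtracting their change could remove real benefit. This stands, and rules out treating the series as a clean control.
- **Not the only comparison.** A reader might infer that this is the trial's sole concurrent series. The complex gastroschisis outcomes and the staggered starts show otherwise.
- **Detail for an analysis plan.** The model itself could reasonably sit there, and its absence here is no fault. The stated single purpose and the limitations list are the protocol's own.

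It might also be argued that spill-over makes a net estimate conservative. Step 4 of the working shows that this is not guaranteed when baseline mortality differs.

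**Conclusion.** The point holds as one of interpretation. A pre-post fall in anorectal malformation and atresia mortality cannot be distinguished from a general improvement in care over time. The protocol names only the favourable reading, and its limitations omit the other. The same improvement would bias the primary unadjusted comparison towards benefit.

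The 21% to 62% figures show how exposed the primary test is to an assumed 5- to 8-point drift. They are not an estimate of this trial's error rate, would apply to any uncontrolled pre-post test of this size, and do not measure what the added analysis would gain. Nor do the documents show that a secular explanation is as likely as spill-over; they show only that the two cannot be separated as planned. This is a worthwhile, inexpensive improvement.

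**What to change.** 1. Where the other-anomaly series is introduced, state both readings in advance: indirect benefit and general improvement over time. Say that a flat series would count as evidence against a general secular improvement.
2. Under Study limitations, add secular trend and the lack of a concurrent control.
3. Add a supporting analysis of the gastroschisis and anorectal malformation/atresia series with site effects, calendar time and each site's own implementation date, using the May to December 2019 stagger. Show the change in each condition side by side with 95% confidence intervals.
4. Describe a fall in the other conditions as consistent with indirect benefit only if it follows site start dates and not calendar time; otherwise report possible secular trend. Note that practice changes before implementation, which the protocol itself anticipates, can blur this distinction.
5. If a net period-by-condition contrast is reported, give it on more than one scale and do not call it conservative.

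**Cost:** the mortality data are already planned, so the change is wording and one added analysis. Intervals will be wide, the stagger gives only about six months of overlap, and the bundle may reach the comparator. The result therefore supports the primary analysis and does not replace it.
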